# The effects of integrating work-related factors and improving cooperation in musculoskeletal physical therapy practice: protocol for the ‘WORK TO BE DONE’ cluster randomised controlled trial

**DOI:** 10.1186/s12891-020-03375-2

**Published:** 2020-06-08

**Keywords:** Musculoskeletal disorders, Physical therapy, Occupational health, Cluster randomised trial

## Abstract

**Background:**

Musculoskeletal disorders (MSDs) are the primary cause of disability worldwide and a major societal burden. Recent qualitative research found that although a patient’s work is considered important, physical therapists take work participation insufficiently into account as a determining factor in the treatment of patients with MSDs. Therefore, the aim of this study is to improve the effectiveness of physical therapy (in primary healthcare) with respect to the work participation of employees with MSDs by increasing the knowledge and skills of generalist physical therapists and by improving the collaboration between generalist physical therapists and physical therapists specialised in occupational health.

**Methods/design:**

This trial is a two-arm non-blinded cluster randomised controlled trial. Working patients with MSDs visiting a physical therapy practice are the target group. The control group will receive normal physical therapy treatment. The intervention group will receive treatment from a physical therapist with more knowledge about work-related factors and skills in terms of integrating work participation into the patients’ care. Data are gathered at baseline (T0), at four months (T1) and eight months (T2) follow-up. Most outcomes will be assessed with validated patient-reported questionnaires. Primary outcomes are the limitations in specific work-related activities and pain during work. Secondary outcomes include limitations in general work-related activities, general pain, quality of life, presenteeism, sick leave (absenteeism), estimated risk for future work disability, work-related psychosocial risk factors, job performance, and work ability. Based on a sample size calculation we need to include 221 patients in each arm (442 in total). During data analysis, each outcome variable will be analysed independently at T1 and at T2 as a dependent variable using the study group as an independent variable. In addition to the quantitative evaluation, a process evaluation will be performed by interviewing physical therapists as well as patients.

**Discussion:**

The trial is expected to result in a more effective physical therapy process for working patients with MSDs. This will lead to a substantial reduction of costs: lower costs thanks to a more effective physical therapy process and lower costs due to less or shorter sick leave and decreased presenteeism.

**Trial registration:**

Netherlands Trial Register, registration number: NL8518, date of registration 9 April 2020, URL registration: https://www.trialregister.nl/trial/8518

## Background

Musculoskeletal disorders (MSDs) are the primary cause of disability worldwide and a major societal burden [1]. MSDs are characterised by pain and reduced physical function, often associated with increased risk of developing other chronic health conditions, increased all-cause mortality, limitations in daily activities, restricted participation, and a significant decline in mental health decline and quality of life [2, 3]. Moreover, MSDs are associated with long-term disability that is often resistant to current treatments [4]. Work-related MSDs are disorders whereby work-related activities and conditions significantly contribute to the onset or progression of the disorder, but are not necessarily the sole cause of the disorder [5]. Whether work-related or not, musculoskeletal complaints can have a significant impact on work in terms of reduced productivity, sickness absence and long-term incapacity to work [6].

Musculoskeletal health is critical to human functioning, enabling mobility, dexterity, and the ability to work and actively participate in all aspects of life. Musculoskeletal health is therefore essential in maintaining human capital as well as economic, social and functional independence across the life course [7]. Work is associated with positive benefits, including both mental and physical health [8]. Social factors such as work, employment and economic status are important health determinants [9], and ‘having a job’ reflects an individual’s ability for functioning as a part of their overall health status [10]. Moreover, the longer individuals are out of work due to MSDs, the harder it is for them to get back to work [11]; early intervention is therefore advocated [12]. In addition, long-term work absence poses a serious risk to physical, mental and social wellbeing, while return to work can improve recovery for individuals with common health problems [8]. Therefore, early discussions about work with individuals are crucial in order to avoid lengthy sick leave which results in fewer treatment gains and greater costs [13].

Although most health professionals, including physical therapists, acknowledge the importance of their patients’ work, occupation and the ability to work, these topics are often not addressed within regular Dutch healthcare [14–18]. Recent qualitative research in the Netherlands found that although a patient’s work is considered important, physical therapists take work participation insufficiently into account as a determining factor in the treatment of patients with MSDs. They often lack specific knowledge about work-related factors, and there is insufficient cooperation between generalist physical therapists and other occupational healthcare providers (including physical therapists specialised in occupational health, occupational therapists and exercise therapists) [18].

In a survey of Dutch physical therapists, 64% of the 142 respondents indicated that occupational factors should be addressed to a greater extent within physical therapy. Only 14.8% of the respondents indicated that they communicate with or consult a physical therapist specialised in occupational health. Only 12.7% of the participants who do not have a specialised physical therapist within their practice sometimes/regularly refer patients to a specialised physical therapist [17]. The participating physical therapists stated that if they communicate with or consult other occupational health professionals, they mainly have contact with occupational health/insurance physicians (72.5%) and occupational therapists (31.7%).

These issues were also seen in qualitative research conducted among general practitioners in the Netherlands which found that general practitioners seemed well aware of the relationship between work and health but needed more knowledge, communication skills and better cooperation with occupational physicians to manage work-related problems. Participants reported that they lacked the knowledge to advise patients specifically concerning their work environment [16].

To redress this imbalance, it is important that healthcare becomes more work-focused [19, 20]. Health professionals need to formulate goals related to work participation, give suitable consideration to work outcomes and manage chronic health conditions to optimise functional capacity [21]. There is robust evidence to suggest that a lack of work-focused healthcare (i.e. the failure of health professionals to address work-related issues in the clinical encounter) is an obstacle to work participation [20]. Work-focused healthcare involves healthcare providers taking an interest in, and accepting responsibility for, addressing obstacles to work participation in the clinical encounter [22].

Important elements in the integration of occupational health into primary healthcare include training primary healthcare professionals to recognise early work-related ill health, to provide advice on improving working conditions and health at work, to support return to work, and to preserve and restore work capacity [21]. Healthcare professionals, including physical therapists, need to take into account patients’ work-related difficulties and their own perceived ability to offer effective guidance, and consider the ‘receptivity’ of employment contexts to patients’ work problems, in order to ensure a smooth transition back to work [14]. Therefore, gaining an understanding of the relationship between health and work should be part of the training of all healthcare professionals [21].

As far as we know, no studies have been conducted in primary healthcare that investigate the effects of work-focused physical therapy for working patients with MSDs. The aim of this study is to improve the effectiveness of physical therapy (in primary healthcare) with respect to the work participation of employees with MSDs by increasing the knowledge and skills of generalist physical therapists and by improving the collaboration between generalist physical therapists and physical therapists specialised in occupational health. The study will consider the following research question: To what extent will integrating work-related factors into the care processes of generalist physical therapists and improving cooperation between generalist physical therapists and physical therapists specialised in occupational health, enhance the effectiveness of physical therapy (in primary healthcare) for working patients with MSDs?

Our hypothesis is that the intervention will result in an increased knowledge of work participation and the relevant factors that influence work participation, which will make it easier to integrate work participation into the care regimen of generalist physical therapists and to decide when referral to or consulting with a physical therapist specialised in occupational health is appropriate. This will improve the effectiveness of care, leading to faster recovery (pain and limitations in activities) and a higher quality of life for patients with MSDs. This also means fewer sessions and reduced recurrences, thus decreasing the costs of healthcare and the costs due to absenteeism and presenteeism.

## Methods/design

### Trial design

This trial is a two-arm non-blinded cluster randomised controlled trial (CRCT). Outcomes are assessed at baseline and at four and eight months after baseline. This protocol complies with the SPIRIT guidelines [23]. The trial will be reported in accordance with the CONSORT guidelines [24]. For the stakeholders involved, this study is entitled: ‘WORK TO BE DONE: integrating work participation into shared decision-making in physical therapy practice’. The short title of the intervention is ‘WORK TO BE DONE’ (in Dutch: WERK AAN DE WINKEL). Figure 1 shows the trial phases and participant flow. Members of the project group ([name]) participated in the design of the trial and the intervention and will participate in each stage of the trial. The advisory group consisting of the relevant stakeholders (see Acknowledgements) provided input on the design of the intervention and will be consulted for advice throughout the trial.

**Fig. 1 Fig1:**
[figure not shown]
Trial phases and participant flow

### Study setting

This is a Dutch CRCT (Trial registration: Netherlands Trial Register: NL8518). The protocol of the study and data management plan have been uploaded to Open Science Framework (https://doi.org/10.17605/OSF.IO/KDUYS). The trial will be conducted in physical therapy practices in the Netherlands. Participating physical therapy practices will be the unit of randomisation (cluster). Working patients with MSDs visiting a physical therapy practice are the target group. The control group will receive regular physical therapy treatment. The intervention group will receive treatment from a physical therapist with more knowledge about work-related factors and more skills in terms of integrating work participation into the patients’ care.

### Participants and recruitment

Participating physical therapy practices will be recruited from among legally registered physical therapists in the Netherlands. Physical therapists in the recruited physical therapy practices can participate in this study if they treat patients with MSDs and do not have a recognised specialisation in the area of occupational physical therapy or work-related physical therapy. Physical therapists will be recruited via announcements made by the stakeholders involved in newsletters and on websites, and via social media.

Patients will be recruited by the participating physical therapists. In order to be eligible for participation in this study, a patient must meet all of the following criteria:
Display one or more musculoskeletal complaintsHave an indication for physical therapy treatmentHave an employment contract or be self-employed (normally working ≥12 h a week)Experience symptoms during work or in their own opinion have problems performing their work (including absenteeism).

Patients who are unable to access and fill in the online follow-up questionnaires will be excluded.

### Randomisation and blinding

The physical therapy practices of the participating physical therapists will be the unit of randomisation (cluster). Each practice will be randomly assigned to either the intervention or control arm on a 1:1 basis. The allocation sequence will be generated online (with a block size of six) [25] using http://randomization.com by the principal investigator. Participating practices will be randomised in the order that they confirm their participation in the study. The practices will be informed about the group allocation by the principal investigator. Based on the randomisation, physical therapists working in the randomised practices will be able to use all the ‘WORK TO BE DONE’ intervention components (intervention group) or will continue providing regular physical therapy to their patients (control group). Physical therapists and patients cannot be blinded to allocation group.

### Procedures

As soon as a physical therapy practice confirms participation in this study, they will receive an email from the principal investigator indicating to which group they have been allocated. All participating physical therapists will receive patient information about the study and materials needed for the inclusion of patients. Patients will be recruited and informed by the participating physical therapy practices. Consecutive patients will be asked if they are willing to participate in this study and will receive the information letter. Patients will be allowed to use all the time they need to consider their participation. As soon as a patient has decided to participate, the first consult will be planned. Patients will also receive an information letter and will be given the time they need to consider their participation. If patients do not want to participate in the study, they will receive regular physical therapy treatment and will not be enrolled in the study. If patients want to participate in the study, the physical therapist will assess them for eligibility during the intake and ask for written informed consent and their contact details. The physical therapist will then send the contact details to the investigators via a secured app (Siilo, Siilo Holding B.V., the Netherlands). An image of the informed consent form will also be sent to the investigators via a secured app. The original form will be sent by regular mail or will be collected by the investigators.

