##### E-learning

Physical therapists must follow an e-learning course consisting of two parts. The first part contains general information about the importance of work-focused healthcare, the interaction between work and health, and (work-related) factors influencing participation in work. The second part contains more specific information and guidance about addressing patients’ work participation in the diagnostic and treatment phase and about working with occupational health professionals, including guidance on cooperation between generalist physical therapists and physical therapists specialised in occupational health.

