### Outcome assessment and data collection

All outcome measures will be self-reported measures. Data will be collected using online questionnaires filled in by the participating patients at the start of the intervention (T0), four months after the start of the intervention (T1, short-term effects) and eight months after the start of the intervention (T2, long-term effects). All questionnaires will be developed using Qualtrics online survey software (Qualtrics®). Outcome measures will be collected from the patients. The schedule for enrolment, outcome measures and time points is summarised in Table 1. Physical therapists will be asked to fill in a questionnaire at the start of the intervention and after eight months.

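### Therapists who already know their practice's arm assess eligibility and take consent at the intake, so the patients entering each arm can differ; T0 very probably follows that contact and should be moved ahead of it

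*Protocol article*

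**What the plan says.** All references are to the Protocol article.

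- **Randomisation and blinding:** "The physical therapy practices of the participating physical therapists will be the unit of randomisation (cluster"). The same section states: "Physical therapists and patients cannot be blinded to allocation group".
- **Procedures:** once a practice has confirmed that it will take part, "they will receive an email from the principal investigator indicating to which group they have been allocated". Recruitment materials and patient recruitment come after that.
- **Participants and recruitment:** "Patients will be recruited by the participating physical therapists". One of the four criteria is "Experience symptoms during work or in their own opinion have problems performing their work (including absenteeism").
- **Procedures, on enrolment:** patients are approached in sequence, receive a letter and may take their time; a first consult is booked once they are willing. Then "the physical therapist will assess them for eligibility during the intake and ask for written informed consent and their contact details". Only after that does the therapist pass the contact details to the investigators.
- **Outcome assessment and data collection:** "Data will be collected using online questionnaires filled in by the participating patients at the start of the intervention (T0").
- **E-learning:** a compulsory course for intervention therapists covers addressing "work participation in the diagnostic and treatment phase".
- **Data analyses:** every outcome at T1 and T2 is adjusted for its own baseline value.

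**The concern.** Cluster randomisation makes the practices comparable. It makes the patients comparable only if the way they are identified and enrolled does not depend on the arm. Here the people who enrol them know the arm, and in one arm they have been trained to ask about work. The Background says that work is often left out of regular Dutch care. A control therapist may therefore probe the work criterion less, and the two arms may enrol patients with different work problems and different prognosis.

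The second issue is the baseline. If a patient completes T0 after meeting a work-focused therapist, the answers may already reflect that meeting. The patient-specific functional scale is the most exposed, because the patient chooses which work activity to rate. T0 is a covariate in every model, so an arm-specific shift in it would pass into the treatment estimate. A larger sample would cure neither problem.

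**Working it through.** **1. Order of events, as far as the text gives it.**

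| Step | Source | Status |
|---|---|---|
| Practice learns its arm | Procedures | Stated |
| Patients approached, letter given, willingness expressed, consult booked | Procedures | Stated |
| Therapist assesses eligibility and takes consent and contact details at the intake | Procedures | Stated |
| Contact details reach the investigators | Procedures | Stated, after consent |
| T0 completed online | Outcome assessment and data collection | Position relative to the intake not stated |

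The first four rows establish the selection risk without inference. The last row needs one. T0 is trial data completed online by participating patients, and consent and contact details exist only from the intake onwards. T0 therefore very probably follows consent and some contact with the therapist. Fig. 1 and Table 1, which would show the exact sequence, are not available.

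**2. The plan's own figure.** The Sample size section gives a difference of 0.7, SD 1.8, two-sided alpha 0.05, power 0.80, ICC 0.05 and 15 clusters per arm.

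- Without clustering: 2 × (1.960 + 0.842)² × 1.8² / 0.7² = 103.8 per arm.
- Design effect with 10 per cluster: 1 + 9 × 0.05 = 1.45; 103.8 × 1.45 = 150.5, that is 15 clusters of 10.
- With 10% more clusters: 15 × 1.1 = 16.5, rounded to 17. At the stated 13 recruited per cluster, 17 × 13 = 221 per arm.

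The stated 221 reproduces and is not in question. It serves only to set a scale.

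**3. Standard error of the difference.** With 17 clusters of 10 completers per arm, the effective n is 170 / 1.45 = 117.2. SE = 1.8 × √(2 / 117.2) = 0.235. This ignores any precision gained from the baseline covariate.

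**4. Selection, illustrated before adjustment.** Bias = share of intervention-arm patients of a kind not recruited in control × their difference in prognosis. Both inputs are assumptions: share 10% to 30%, prognosis difference 0.5 to 1.0 point.

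- Low: 0.10 × 0.5 = 0.05 points; 0.05 / 0.7 = 7%.
- High: 0.30 × 1.0 = 0.30 points; 0.30 / 0.7 = 43%.

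The next table shows what a bias b would do if that much remained **after** adjustment. False-positive rate = P(|Z + b/SE| > 1.96). Power with the bias against the intervention = Φ((0.7 − b)/SE − 1.96).

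| b (points) | Share of 0.7 | False-positive rate | Power if b acts against the intervention |
|---|---|---|---|
| 0 | 0% | 5% | 85% |
| 0.1 | 14% | 7% | 72% |
| 0.2 | 29% | 14% | 57% |
| 0.3 | 43% | 25% | 40% |

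**5. A shifted T0, illustrated.** If the intake moves T0 by d in one arm only, and the baseline-outcome slope is β, baseline adjustment moves the estimate by β × d. Assume d from 0.2 to 0.5 points and β from 0.3 to 0.7.

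- Low: 0.3 × 0.2 = 0.06 points (9% of 0.7).
- High: 0.7 × 0.5 = 0.35 points (50% of 0.7).

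This covers only a shift in the T0 score. It does not cover any effect on later scores of having chosen a different activity.

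**The case against.** The other side has several fair points.

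- **T0 timing is inferred.** A reader might conclude that T0 can only come after the intake. The text does not establish that. Consent is taken during the intake, not at its end, and the figure and table with the schedule are missing. What stands is a strong inference that T0 follows consent and first contact.
- **Contamination of both primary outcomes is a tempting stronger reading.** Both measures look back over the previous week, most of which precedes the intake, so one consult is unlikely to change a past-week pain rating much. The e-learning syllabus also does not say that the intake delivers the intervention. What remains plausible is an effect on which work activity is chosen and how it is rated.
- **The work criterion belongs to the patient.** It rests on the patient's own view, and symptoms at work are enough to meet it. Contract and hours are factual. This narrows the therapist's discretion but does not remove it, because the therapist elicits the answers and decides at the intake.
- **Safeguards exist.** Patients are approached consecutively and express willingness before the consult is booked; T0 is self-completed and the analysis is blinded. Nothing suggests that the letter differs by arm. These reduce the risk, but none hides the allocation from the person who enrols.
- **Adjustment would absorb part of the bias.** The baseline covariate and the 10% change-in-coefficient rule can deal with measured differences. They cannot deal with unmeasured ones, or with a T0 that has itself been shifted.
- **A screening log may be in the fuller documents.** The article points to a protocol and data management plan held elsewhere and promises CONSORT reporting. Its absence here is not a defect in itself.

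**Conclusion.** The selection risk holds on the stated text. Allocation is known before recruitment, and the same unblinded therapists assess eligibility and take consent, so the patients in the two arms can differ despite cluster randomisation. The documents do not show that they will differ, or in which direction.

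The baseline part holds in a limited form. T0 very probably follows consent and first contact. That matters chiefly for the patient-chosen work activity and its rating, and less for past-week pain.

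The 0.05 to 0.30 points (7% to 43% of 0.7) is an illustration before adjustment. Its inputs, a 10% to 30% share and a 0.5 to 1.0 point difference in prognosis, are not from the protocol. It should not be read as the residual bias of the planned analysis. The lower end is minor; a residual bias near the upper end would be serious. The case for acting is that the change is cheap now and that analysis cannot reliably repair the problem after recruitment.

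**What to change.** Amend the Procedures section so that three things happen at the existing information-letter step, before the first consult:

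1. The patient reports the work-related eligibility items online: employment status, hours, and symptoms or problems at work.
2. The patient gives consent and contact details.
3. The patient completes T0 online.

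The letter and form should be identical in both arms and should not reveal the practice's arm. At the intake the therapist then only confirms the indication for physical therapy. State explicitly in the text that T0 precedes the first consult; if Fig. 1 or Table 1 already shows this, bring the Procedures section into line with it.

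As support, have each practice count the consecutive working patients invited, eligible and consenting, and report these by arm.

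**Cost:** a small procedural amendment, one online form and the practice counts. Some patients will complete T0 and then prove to have no indication. The judgement of indication stays with a therapist who knows the arm, so the change reduces the selection risk without removing it; the counts by arm help to show what is left. The sample size is unaffected.
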